#### Children’s general health

Weight is measured to the nearest 0.1 kg (Weighing Scale 803, Seca, Hamburg, Germany) and height is measured to the nearest 0.1 cm (Stadiometer 213, Seca, Birmingham, United Kingdom). Children are measured with light clothing and no shoes. BMI *Z*-scores are calculated using Dutch reference values [32]. The primary outcome measure is the absolute change in BMI *Z*-score, as we aim for BMI scores closer to the national and international standards with smaller standard deviations, which will be reflected in a decrease of BMI in overweight and obese children and an increase of BMI in underweight children. Hip and waist circumferences are measured with a measuring tape to the nearest 0.1 cm, following the World Health Organization’s assessment protocol (model 201, Seca, Hamburg, Germany) [33]. Handgrip strength is measured with a calibrated Jamar hydraulic hand dynamometer (model 5030 J1, Jamar, Huthwaite, United Kingdom) to the nearest 0.5 kg [34]. All anthropometric measurements are performed twice, and a third measurement is conducted if the difference between the first two measurements exceeds a pre-set limit (weight ≥ 0.2 kg, height ≥ 0.5 cm, hip and waist circumference ≥ 1.0 cm, handgrip strength ≥ 1 kg).

Disease status since birth, hospital admissions (number and duration), healthcare visits (number), and medication use in the previous 12 months are measured by the online parental questionnaire. The wording of all disease status items are based on a questionnaire used in a previous study, tailored to the school-age population [35]. Blood pressure measured between the ages of 4 to 6, birth weight and additional information on disease status are obtained from the regular GGD measurements.

#### Children’s health-related quality of life and psychosocial functioning

The validated EuroQol 5-Dimensions Youth version questionnaire (EQ-5D-Y) and the proxy version for parents are used to measure children’s HR-QoL [36]. Child-specific HR-QoL is measured by the validated Paediatric Quality of Life Inventory (PedsQL) and parents complete the proxy version of this questionnaire [37, 38]. Psychological attributes (emotional symptoms, conduct problems, hyperactivity/inattention, peer relationship problems and prosocial behaviour) are measured by means of the Strength and Difficulties Questionnaire, a well-validated index of psychosocial functioning in children [39, 40].

Social, emotional, and academic self-efficacy is assessed in younger children using three questions from the Self-Efficacy Questionnaire for Children (SEQ-C), which is rated using a Manikin scale [41, 42]. Children in groups 7–8 complete the full 24-item version of the SEQ-C [42]. Self-confidence, social skills, self-efficacy, school well-being, future expectations, and social support are measured by the OnderwijsMonitor Limburg programme.

#### Children’s physical activity behaviour

Physical activity levels are assessed objectively using the Actigraph accelerometer (Actigraph, GT3X+, Actigraph, Pensacola, United States). The monitor is attached to the right hip with an elastic band. All children are instructed to wear the device for seven consecutive days. The device should be worn all day except during sleeping hours and activities involving water (e.g., swimming, bathing, or showering). In the same week, parents fill in a short activity diary on their child’s physical activity and swimming behaviour and exceptional circumstances (e.g., illness of the child). In each participating school, ten randomly selected children in group 5 are equipped with a second activity monitor for 1 week, the ActivPal accelerometer (VTaP, ActivPal, Glasgow, Scotland). This accelerometer is attached to the right upper leg using tape. The ActivPal accelerometer measures postural allocation more accurately than the Actigraph, enabling us to detect sedentary behaviour patterns in more detail [43].

During PE lessons, children perform a 20-m shuttle run test, better known as the Progressive Aerobic Cardiovascular Endurance Run (PACER) as a measure of their cardiorespiratory fitness [44]. Children are encouraged to continue the test until exhaustion. Children do not perform the shuttle run test while wearing the accelerometer, as the aim is to measure usual activity patterns during a regular school week. Self-reported sports club membership, active forms of transport to school, and leisure time physical activities (e.g., children’s activities in weekends: watching TV, music or theatre, playing outdoors, practicing sports etc.) are assessed in both children and parents.

#### Children’s dietary behaviour

Food intake is measured by a combination of a food frequency questionnaire and a dietary recall tool to be completed by both children and parents. The food intake questionnaire was designed for this target group based on two questionnaires developed by Van Assema et al. [45, 46]. Items of this questionnaire include fruit and vegetables, soft drinks, sports and energy drinks, and snacks. Dietary recall is used to assess the composition of breakfast and lunch. The questions about lunch intake are asked in the classroom immediately after the lunch break. Children are not pre-informed that they are going to be asked about dietary consumption, to avoid a potential effect of the questionnaires on children’s dietary patterns.

In addition, food preferences and familiarity with healthy food products are assessed. The questions mainly consist of pictures of food items, for which children can indicate whether they have ever eaten these items and whether they like them or not. These questions were developed based on an existing instrument previously used in the INPACT study [47].

#### Household characteristics

Parental BMI is assessed by self-reported height and weight of both parents/caregivers. Parental practices regarding nutrition are determined by a shortened version (nine items) of the Comprehensive Snack Parenting Questionnaire (CSPQ) [48]. Parental practices regarding physical activity are assessed by a questionnaire developed in the same style as the CSPQ. Parental well-being and HR-QOL are measured by the Satisfaction With Life Survey (SWLS) questionnaire and the EuroQol – 5-Dimensions Questionnaire (EQ-5D), respectively [49, 50].

Labour participation of parents is assessed by current employment status. Current employment status is combined with parental education level and household income to determine SES. All questions about SES have been derived from previous, large-scale Dutch studies, including those specifically addressing socio-economic inequalities in health [51–53]. In addition, parents are asked about their ethnicity and level of (material) deprivation [54]. Parental sick leave and absence from work or education because of illness of their child is also included in the online questionnaire. Labour participation is combined with parental sick leave rates to determine productivity losses from work.

#### Teacher-related variables

Teacher’s self-reported weight and height and transport forms to work are assessed by means of a written questionnaire. School practices regarding nutrition and physical activity (e.g., modelling eating healthy food products and encouraging children’s physical activity) are determined by an adapted version of the Parental Practices Instrument.

#### Children’s academic achievements

Academic performance is monitored using the *Centrale Eindtoets Basisonderwijs* (CITO), and various other tests used by the schools [http://www.cito.com/about_cito/history_of_cito]. In the Netherlands there is a long tradition of testing at the end of primary school to support the decision in which track children will continue their secondary education. Since 2015, participation in these tests is obligatory by law. All schools participating in the study are currently using the standard version, although schools can opt for a few alternative tests. The test measures language, maths and world orientation. In addition to this end of primary school test, many schools use a wide range of tests throughout the children’s school careers. This also includes tests on mathematics (taken twice a year) and various aspects of language such as decoding skills, spelling, vocabulary, and reading comprehension. With the exception of the two partial intervention schools, the schools in this study are using a wide range of such tests, which are – using the data from OnderwijsMonitor Limburg – also comparable to those used in other schools in the region.

The secondary school advice provided by the primary school, the actual level of secondary school opted for (Dutch secondary education is hierarchically ordered), the school absenteeism and repeating years are assessed for all participating children via the schools.

#### Process evaluation

General parental satisfaction with their children’s school (including safety, communication, quality of education, challenges to children, and professionalism of teachers) are assessed using a school satisfaction questionnaire, which is regularly used in the Dutch school system. Implementation of the intervention is evaluated by qualitative outcome measures such as interviews with parents and children, and classroom observations.

In the Netherlands, parents are free to choose which school their child attends. The introduction of the intervention might therefore influence their choice of school and thus change the composition of the sample. Distance is an important determinant of school choice [26]. A simulation using the model of Borghans et al. shows that the effect on the enrolment is expected to be rather small [26]. The data provided by the OnderwijsMonitor Limburg allows us to investigate the actual choice patterns and outcomes for the schools in the region. In addition, head teachers are asked if the presence of the intervention influenced the new school entries.

#### Evaluation of legal aspects

The research questions on legal aspects will be addressed by a thorough scientific literature study and examination of policy and legislation instruments and case-law on the scope of children’s right to health. The literature study will focus on the right to health, evaluation of the scope of this right, and the right to health of children in particular. In addition, literature and case-law research will be conducted to explore the existing conflicting interests of parties involved in the realization of children’s right to health, particularly in healthy school settings. Interviews will be held to determine the interests of the different parties involved in the healthy school setting. In addition, a comparison will be made with the legal situation in Scotland, in view of the embedding of the healthy school concept in the Scottish legal (educational) system. Conflicts of interest regarding the realization of children’s rights to health and education in the healthy school setting will be explored and resolved using a legal theoretical framework. In addition, the Scottish model will be used to identify and resolve the conflicts of interest.

### Statistics

#### Sample size calculation for primary research question

The primary sample size calculation is based on the primary outcome, i.e. detecting a difference in mean absolute BMI *Z*-scores between participants in the two full-intervention schools and participants in the four control schools, after 4 years of intervention. All assumptions are shown in Table 4.

**Table 4 Tab4:** Assumptions of the sample size calculation

Sample size calculation assumption
100 participants per school
2 full intervention, 2 partial intervention and 4 control schools
Participants of cohorts F, G, H, and I will be included (Table 1)
A significance level (alpha) of 0.05
A power of 80 %
Independent-samples *t*-test on difference in absolute BMI *Z*-scores
An intraclass correlation coefficient of 0.01, as based on Amorim et al. [64]
Unequal cluster sizes with a relative efficiency of 90 % [65]
A dropout rate of 20 % (including both study drop-out and natural drop-out such as migration)
An average absolute BMI *Z* of 0.76 and an SD of 0.60 in the population (these values were calculated over all children aged between 4 and 11 living in Parkstad region who visited the Youth Health Services in 2013).

With these assumptions we should be able to detect a difference in mean absolute BMI *Z*-score of 0.24 between the full-intervention and control groups, which correspondents to a medium standardized effect size (Cohen’s *d* of 0.41). Detecting this difference is feasible in this population, as a school-based longitudinal study with comparable intervention components found a mean difference between the intervention and control groups of −0.26 (CI 95 %: −0.32, −0.21) BMI *Z*-score [55].

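### The detectable differences allow for clustering but not for there being only six or four schools, so 80% power is overstated for the endpoint t-test on which it is based

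*Protocol article*

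**What the plan says.** Table 4 of the protocol article, under the sample size calculation for the primary research question, lists the inputs: "100 participants per school"; "2 full intervention, 2 partial intervention and 4 control schools"; "A significance level (alpha) of 0.05"; 80% power; an independent-samples t-test on absolute BMI Z-scores; "An intraclass correlation coefficient of 0.01"; "Unequal cluster sizes with a relative efficiency of 90" per cent; "A dropout rate of 20" per cent; and a mean of 0.76 "and an SD of 0.60 in the population".

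From these the primary section concludes "With these assumptions we should be able to detect a difference in mean absolute BMI" Z-score of 0.24 (d = 0.41). It calls this feasible because a comparable school study found a difference of 0.26 in size (95% CI 0.21 to 0.32). The section for the secondary question uses the same inputs, obtains 0.28 (d = 0.47), and argues from a meta-analysis that differences of up to 0.28 are likely.

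The data analysis section plans a three-level mixed model with group, time and their interaction as fixed effects, random school and participant effects, and baseline covariates where relevant.

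**The concern.** Whole schools receive the full, partial or control condition, so a comparison of conditions is a comparison of schools. A design effect enlarges the variance for similarity within schools. It does not allow for the fact that the variation between schools must be estimated from very few of them. Six schools in two groups leave 6 - 2 = 4 df, and four schools leave 4 - 2 = 2. The two-sided 5% critical values are then 2.776 and 4.303, compared with 1.96 for large samples.

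If the stated figures rest on the large-sample value, the quoted power is too high for the test it describes. A null result would be read as evidence against effects of 0.24 or 0.28 that the stated test would often miss. The feasibility argument for each question would also lose its basis.

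**Working it through.** **Inputs.** All are from Table 4: 100 children per school; 2, 2 and 4 schools; ICC 0.01; relative efficiency 0.90; dropout 20%; SD 0.60; alpha 0.05; power 80%. Sidedness is not stated; two-sided is assumed because it reproduces the published figures.

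**Step 1: effective sample size.**
Design effect = 1 + (100 - 1) × 0.01 = 1.99.
Effective n per school = 100 × 0.80 × 0.90 / 1.99 = 36.18.

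**Step 2: standard errors**, SE = 0.60 × √(1/n1 + 1/n2).
- Primary, 2 v 4 schools: n = 72.4 and 144.7, SE = 0.0864.
- Secondary, 2 v 2 schools: n = 72.4 and 72.4, SE = 0.0997.

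**Step 3: reproduce the plan's figures.** With (1.96 + 0.84) × SE, the detectable differences are 0.242 and 0.280. A t-test with participant-level df (about 215 and 143) gives 0.243 (d 0.405) and 0.281 (d 0.469). Both routes match the stated 0.24 and 0.28, so the reference distribution used is effectively normal.

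**Step 4: same SEs, between-school df.** The noncentrality is 0.24 / 0.0864 = 2.78 (primary) and 0.28 / 0.0997 = 2.81 (secondary). Power comes from the two-sided noncentral t. The detectable difference is the noncentrality needed for 80% power (3.76, 5.65 and 3.51 for 4, 2 and 5 df) times the SE. One model of all eight schools in three groups has 8 - 3 = 5 df.

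| Comparison | Schools fitted | df | Critical value | Power at stated difference | Detectable at 80% | d |
|---|---|---|---|---|---|---|
| Primary, 0.24 | 6 | 4 | 2.776 | 55.7% | 0.325 | 0.54 |
| Primary, 0.24 | 8 | 5 | 2.571 | 60.8% | 0.304 | 0.51 |
| Secondary, 0.28 | 4 | 2 | 4.303 | 35.3% | 0.564 | 0.94 |
| Secondary, 0.28 | 8 | 5 | 2.571 | 61.6% | 0.351 | 0.58 |

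**Step 5: other readings of the inputs.**
- Taking the design effect on the 80 children left after dropout (1.79) gives 60% and 38% with 4 and 2 df, or 65% and 66% with 5 df.
- Dropping both the dropout and unequal-size allowances, with the design effect on 100, gives SEs of 0.0733 and 0.0846. Power is then 69% and 44% with 4 and 2 df. With 5 df the noncentralities are 0.24 / 0.0733 = 3.27 and 0.28 / 0.0846 = 3.31, still short of 3.51.
- One-sided testing at 5% on the stated inputs gives 74% and 57% with 4 and 2 df.
- For an assumed ICC of 0.005 to 0.02, power runs from 67% to 41% (4 df) and from 43% to 27% (2 df).

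**Step 6: the feasibility sentences.** The restated primary detectable difference, 0.30 to 0.32, exceeds the 0.26 cited in support. At 0.26, power is 62% with 4 df and 67% with 5 df. The restated secondary detectable difference, 0.35 to 0.56, exceeds the 0.28 that the plan treats as the upper end of what is likely.

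**The case against.** The strongest reply is that the planned analysis is not the test in Table 4. The mixed model uses baseline and yearly measurements, which can reduce variance. Suppose baseline adjustment multiplies the variance by 1 - r². This is an illustration, as the document gives no within-child correlation r. For r = 0.5, 0.6, 0.7 and 0.8, primary power at 0.24 with 4 df becomes 67%, 74%, 82% and 93%. Secondary power at 0.28 with 5 df becomes 74%, 80%, 88% and 96%; with 2 df it stays between 43% and 67%. This stands as a limit on the point. A reader might infer that the mixed model itself has only 56% or 35% power, and the document does not support that. But the plan claims no such gain: its 80% rests on the unadjusted endpoint t-test.

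Three other strong readings go too far.

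- **That clustering was ignored, or the sums are wrong.** The plan applies a design effect of 1.99 and a further 10% loss for unequal schools, and its arithmetic reproduces. Only the allowance for few schools is missing.
- **That secondary power is simply 35%.** That holds only if full versus partial is fitted on four schools alone. The plan does not say so, and one eight-school model gives 62%.
- **That the analysis will inflate the type I error.** A t statistic on 4 or 2 df exceeds 1.96 in about 12% or 19% of null cases, but the plan does not say it will use 1.96. The df method may properly be left to a statistical analysis plan.

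It is also true that with only the random school effect described, a stable school difference cancels from change over time. Kenward-Roger or Satterthwaite df for group-by-time would then not generally be 4 or 2. That bears on the remedy. It does not rescue the published power figures, which come from a comparison at the end of follow-up.

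**Conclusion.** The point holds for the sample size statement as printed. For the endpoint t-test in Table 4, 80% power at 0.24 and 0.28 is obtained only by treating the reference distribution as normal or participant-level. With between-school df, power is about 56% to 61% (primary) and 35% to 62% (secondary), the range depending on whether each comparison uses its own schools or one eight-school model. The corresponding detectable differences are about 0.32 or 0.30, and 0.56 or 0.35. No two-sided reading of the stated inputs tried here reaches 80%.

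These results assume two-sided 5% testing, the plan's ICC of 0.01, its SD of 0.60, and no credit for baseline or repeated measures. They do not establish the power of the longitudinal model.

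**What to change.** 1. Restate the power, or the detectable differences, with between-school df for the model that will be used, and say which: about 0.32 and 0.56 if each comparison uses its own schools, or 0.30 and 0.35 for one eight-school model.
2. Revise the two feasibility sentences that rely on 0.24 and 0.28.
3. If credit is taken for baseline or repeated measures, state the assumed within-child correlation and show the result over a range.
4. In the mixed model, add a school-by-time random term and test the group-by-time contrast with small-sample df (Kenward-Roger or Satterthwaite). Analysing school-level mean changes would be equivalent. Naming a df method without the school-by-time term would not generally give the df behind the restated figures.

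No extra schools or children are needed. The cost is a rewrite of the sample size text, one added model term, less favourable stated figures and wider confidence intervals.

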#### Sample size calculation for secondary research question

To detect differences between the two full-intervention schools and the two partial-intervention schools, a second sample size calculation was performed. The assumptions used are shown in Table 4. With these assumptions we should be able to detect a difference in mean absolute BMI *Z*-score of 0.28 between full intervention and partial intervention, corresponding to a medium standardized effect size (Cohen’s d = 0.47). Based on the meta-analysis by Waters et al., it is likely that changes between full intervention and partial intervention of up to 0.28 can be found [56].

#### Data analysis for primary and secondary research questions

Linear mixed model analysis techniques will be used to assess the longitudinal effect of the intervention on the primary outcome measure of absolute BMI *Z*-scores. This technique corrects for correlations within individuals within groups, which occurs in this type of repeated-measures research design. Another advantage of this technique is that it naturally handles missing values in the outcome (likelihood-based method), as long as data are missing at random. Since measurements are repeated within participants, who are nested within schools, we will use a three-level model with schools as the third level, participants as the second level and measurements as the first level. The fixed part of the model consists of group (intervention versus control), time (time points at which the measurements are taken) and the interaction term group*time. Baseline variables that are related to missing data or outcomes will also be included to obtain unbiased results and/or to gain precision. As for the random part of the model, a random school and participant effect will be included in addition to the repeated measurements. For the repeated measurements, the covariance structure will be chosen based on Akaike’s Information Criterion. All participants with at least one outcome measurement will be included in the analysis.

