**Methods:**

In close collaboration with various stakeholders, a quasi-experimental study was developed, for which children of four intervention schools (*n* = 1200) in the southern part of the Netherlands are compared with children of four control schools (*n* = 1200) in the same region. The interventions started in November 2015. In two of the four intervention schools, a whole-school approach named ‘The Healthy Primary School of the Future’, is implemented with the aim of improving physical activity and dietary behaviour. For this intervention, pupils are offered an extended curriculum, including a healthy lunch, more physical exercises, and social and educational activities, next to the regular school curriculum. In the two other intervention schools, a physical-activity school approach called ‘The Physical Activity School’, is implemented, which is essentially similar to the other intervention, except that no lunch is provided. The interventions proceed during a period of 4 years. Apart from the effectiveness of both interventions, the process, the cost-effectiveness, and the expected legal implications are studied. Data collection is conducted within the school system. The baseline measurements started in September 2015 and yearly follow-up measurements are taking place until 2019.

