We present a study protocol that examines the effectiveness of two novel, integrated healthy school interventions. One is a full intervention called ‘The Healthy Primary School of the Future’, the other is a partial intervention called ‘The Physical Activity School’. These intervention approaches will be compared with the regular school approach that is currently common practice in the Netherlands. We hypothesize that these healthy school interventions will result in normalized BMI distributions that are more in line with national and international standards (smaller standard deviations) among primary school children, with a more pronounced effect in the full intervention schools (due to the expected synergy between exercise and diet) than in the partial intervention schools. Also, our multi-disciplinary research group will study a wide range of outcome measures, including lifestyle behaviours, academic achievement, child well-being, socio-economic differences, and societal costs. Moreover, an evaluation will be performed of the legal consequences of a healthy school approach in the Netherlands, as well as the conflicting interests of the stakeholders.

Our primary research question is: What is the effect of the full intervention (‘The Healthy Primary School of the Future’) on the BMI of primary school children compared to no intervention (control schools)? Our secondary research question is: What is the effect of the full intervention on the BMI of primary school children compared to the partial intervention (‘The Physical Activity School’)?

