## Methods

### Setting and study design

The current study has a quasi-experimental design with four intervention schools and four control schools. All participating schools are primary schools situated in the Parkstad region in the Province of Limburg, in the southern part of the Netherlands. This is a relatively poor region with a low SES in which unhealthy lifestyles are highly prevalent [23, 24]. Overweight and obesity rates are substantially higher than the national average in the Netherlands [25]. The intervention schools and control schools are both members of the MOVARE educational board. In the Dutch primary school structure, pupils successively follow eight ‘groups’, starting in group 1 at the age of 4 and typically proceed to secondary school at the age of 11 or 12. Internationally, the first two groups are comparable to pre-school and the last six groups are comparable to grades 1–6.

Two schools take part in the full intervention named ‘The Healthy Primary School of the Future’. Two other schools implement the partial intervention named ‘The Physical Activity School’ (Fig. 1). No randomization was applied, because full voluntary cooperation and participation of the intervention schools is required for the implementation of the interventions. The population consists of a dynamic cohort comprising children in groups 1–8 (Table 1). Baseline measurements were conducted in September-October 2015, and yearly follow-up measurements will take place until 2019. The intervention started in November 2015.

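### The two-level group term has no full-versus-partial comparison and, read literally, averages the full and partial effects in the primary comparison

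*Protocol article*

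**What the plan says.** The Background poses two questions about BMI. The primary one concerns the effect of the full intervention on "BMI of primary school children compared to no intervention (control schools"). The secondary one is "What is the effect of the full intervention on the BMI of primary school children compared to the partial intervention". The hypothesis is a benefit of both interventions, "with a more pronounced effect in the full intervention schools".

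The primary sample-size section sizes the comparison "between participants in the two full-intervention schools and participants in the four control schools". The secondary section sizes the two full against the two partial schools.

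The analysis section is headed "Data analysis for primary and secondary research questions" and gives a single model for both. Its group term reads: "The fixed part of the model consists of group (intervention versus control"). Time and group-by-time complete the named fixed terms, with baseline covariates added where needed. Everyone with at least one outcome measurement is included, and no restriction to a subset of schools is stated.

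On what counts as an intervention school, Setting and study design says: "The current study has a quasi-experimental design with four intervention schools and four control schools". The Abstract says: "In the two other intervention schools, a physical-activity school approach called ‘The Physical Activity School’, is implemented".

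The section on the tertiary questions applies the same model to numerical outcomes and a logistic analogue to categorical ones.

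**The concern.** A two-level factor cannot carry two contrasts among three groups. The article uses the term intervention schools for all four non-control schools, and when it means only the two full schools it normally says so. With all participants included and a group variable that takes only two values, children in partial schools would be coded as intervention. The group-by-time coefficient would then describe a mixture of the two programmes, which neither research question asks about, and the model would contain nothing that separates full from partial.

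The primary result is at stake under that reading. If partial works less well than full, as the article expects, the coefficient understates the full effect. The secondary question is at stake under any reading of the bracket. The tertiary outcomes inherit the problem, because the first tertiary question also compares full with partial and with control.

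**Working it through.** **1. What each part of the article needs from the group term**

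| Place | Comparison |
|---|---|
| Background, primary question | full v control |
| Background, secondary question | full v partial |
| Primary sample size | 2 full v 4 control schools |
| Secondary sample size | 2 full v 2 partial schools |
| Data analysis, group term | intervention v control |

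**2. Which contrast the stated detectable differences belong to**

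Inputs from Table 4: 100 participants per school; 2, 2 and 4 schools; SD 0.60; ICC 0.01; relative efficiency 0.90; dropout 20%; alpha 0.05; power 80%. Sidedness is not stated, so two-sided is assumed.

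- Numbers after dropout: full 200 × 0.8 = 160; partial 160; control 400 × 0.8 = 320.
- Design effect: (1 + 99 × 0.01) / 0.90 = 1.99 / 0.90 = 2.211.
- Detectable difference: 0.60 × √[2.211 × (1/n1 + 1/n2)] × (1.960 + 0.842).

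| Contrast | n1, n2 | Computed (normal) | Computed (t) | Stated |
|---|---|---|---|---|
| Full v control | 160, 320 | 0.242 | 0.243 (d 0.405) | 0.24 (d 0.41) |
| Full v partial | 160, 160 | 0.280 | 0.281 (d 0.469) | 0.28 (d 0.47) |
| Pooled v control | 320, 320 | 0.198 | 0.198 (d 0.330) | none |

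Both stated figures reproduce. They belong to the two separate contrasts. The contrast that the model literally contains has a different detectable difference, which the article does not give.

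**3. What the literal model would estimate**

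With equal numbers in the full and partial schools, as Table 4 assumes, the pooled effect is (full + partial) / 2. The article gives no partial effect, so it is assumed over a range. The full effect is set at the stated detectable difference of 0.24. The standard error of the pooled contrast is 0.60 × √(2.211 × 2/320) = 0.0705, and power is Φ(effect / 0.0705 − 1.960).

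| Assumed partial effect | Pooled effect | Power |
|---|---|---|
| 0 | (0.24 + 0) / 2 = 0.12 | about 40% |
| 0.12 | (0.24 + 0.12) / 2 = 0.18 | about 72% |
| 0.24 | (0.24 + 0.24) / 2 = 0.24 | about 93% |

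For comparison, full v control at 0.24 has power of 79.3% on the same assumptions. These figures use the article's own t-test framework, not the repeated-measures model, and keep the ICC at 0.01.

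**4. The alternative reading**

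If the bracket means full v control in a run limited to those six schools, the group-by-time term answers the primary question and step 3 does not apply. The secondary question compares two groups, neither of which is control: the Background equates control with no intervention, and the partial schools have one. The stated term therefore does not describe that comparison.

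**The case against.** The strongest defence is that pooling is nowhere stated. The research questions and both sample-size calculations point to two pairwise comparisons, and the analysis section speaks of the intervention in the singular. The bracket may be shorthand for the two groups in whichever comparison is being run. A condensed article may also leave contrast coding to an analysis plan that is not shown.

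Much of this stands. A reader might infer that the plan definitely pools the two programmes and so answers neither question. The documents do not support that as fact: pooling follows from the literal wording and the article's usage, and the shorthand reading would answer the primary question. The dilution figures are therefore conditional.

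Two further inferences are also unsupported.

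- The 0.26 difference cited as a benchmark should not be used to size the dilution. It is reported as a difference in BMI Z-score, whereas the trial outcome is the absolute BMI Z-score.
- A gain in between-school degrees of freedom from a three-group model should not be claimed. A gain exists only relative to separate pairwise fits; the pooled model would have 8 − 2 = 6, against 8 − 3 = 5 with three groups. It also need not apply to a group-by-time term in a model without a school-by-time effect.

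The defence does not remove the conflict. The shorthand reading goes against the article's use of intervention schools and its inclusion of all participants, and it still supplies no wording that fits full v partial. Nor is this detail left for later: the article fixes the group term, and in a form that does not match its own questions.

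**Conclusion.** Wrong as written. The stated group term conflicts with the secondary question on either reading, and with the primary question on the literal one. The first conclusion needs no numerical assumption.

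The size of the second depends on the literal reading, equal numbers in full and partial schools, and a partial effect that the article does not supply. Over the range shown, an effect of 0.24 in the full schools would appear as anything from 0.12 to 0.24. It is undistorted only if partial works as well as full, which the article does not expect.

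The fault lies in the analysis wording. The sample-size figures are consistent with the intended contrasts and need no change on this account.

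**What to change.** In the analysis section, replace the two-level group term with a three-level factor (full, partial, control) and its interaction with time, fitted to all eight schools. Name full v control as the primary contrast and full v partial as the secondary contrast. Make the section on the tertiary questions refer to the same factor.

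The cost is one sentence, with no change to data collection or to the stated detectable differences. The small downside is that a single model assumes common variance components across the three groups. Separate pairwise models, each explicitly restricted to the schools being compared, would also resolve the conflict if the trial team prefers them.
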